### Feasibility

The first aim of this study is to determine feasibility and acceptability. Measures of feasibility are (1) enrollment (number of participants consented and enrolled) and (2) randomization (percentage of patients enrolled who are randomized). Participant-level measures of feasibility include (1) attendance (percentage of sessions attended by each MBI participant), (2) intervention completion (percentage of total intervention sessions attended by each MBI participant), and (3) assessment completion (percentage of completed patient-reported assessments at each time point). Failure to complete measures within 2 weeks of recruitment (baseline) or MBI sessions 1, 3, and 6 results in missing data for that time point.

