### Randomization procedures

Patients who provide informed written consent and meet the participant selection criteria will be enrolled and randomized using a 2:1 treatment allocation to either the MBI or control condition. Because the MBI condition is group-based, randomization of participants will be divided into 4 cohorts of 15 participants to reduce the amount of idle time between informed consent and intervention delivery. After the first cohort of 15 participants provides informed consent, they will be randomly assigned either to receive the MBI (*n* = 10) or to a control condition (*n* = 5). The random number function in Excel 2007 software (Microsoft, Redmond, WA, USA) will be used to randomize patients to either the MBI (*n* = 40) or control (*n* = 20) condition using a permuted block randomization scheme to achieve a 2:1 allocation. Within each block size of 15, 10 patients will be randomized to receive the MBI and 5 will be randomly assigned to the wait-listed control condition.

Within 2 weeks of randomization, participants will begin the MBI or their time in the control condition. Following randomization and initiation of the first cohort of 15 patients, the next cohort of 15 patients will be recruited and randomized following the same protocol. This will continue until 60 participants are randomized in a total of 4 cohorts.

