### Retention strategies and compensation

In an attempt to prevent participants from dropping out before the MBI starts, a proactive retention strategy will be used to retain participants who have been randomized but have not yet participated in the MBI. Participants will receive weekly contact via telephone and email and will be provided with information regarding how many more participants are needed before the intervention will begin. After beginning the MBI program, participants randomized to the MBI will receive either a telephone call, a text message, or an email (their choice) on the morning of each mindfulness session and again 1 h before each session. In addition, all participants will receive weekly and biweekly contact from study personnel to remind them of their study participation, upcoming due dates for assessments, and when compensation checks have been mailed to their home address.

Three monetary payments will be provided to help increase retention and compensate participants for their time: (1) $10.00 after baseline assessments are received and/or participation in MBI session 1 has occurred, (2) $20.00 after receiving measurements at the end of week 3 and/or participation in MBI session 3, and (3) $30.00 at the conclusion of the study upon receiving the final measurements and/or participation in MBI session 6. All subjects in the in MBI and control groups will receive payments upon return of each assessment according to this schedule. In addition to providing monetary compensation, the MBI program will be provided at no cost to subjects, a value of over $400.00.

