### Efficacy

To address aim 2, five valid and reliable patient-reported questionnaires will be administered to determine the effects of MBI relative to the control condition on pain catastrophizing, as well as on pain interference and severity, depression, health-related quality of life (mental and physical health), and mindfulness (Table 3). Each questionnaire will be administered at four time points: week 0 (baseline, prior to initiation of treatment) and weeks 1, 3, and 6. Assessments at weeks 1, 3, and 6 correspond to MBI session 1, session 3, and session 6, respectively.

**Table 3 Tab3:** Instruments and schedule of assessments

Instrument	Abbreviation	Domain	Scale/subscale reliability (Cronbach’s α)	Interpretation^a^	Baseline	Week 1	Week 3	Week 6
Demographic Questionnaire	DEMO	Sociodemographic and clinical characteristics	N/A	N/A	X			
Pain Catastrophizing Scale	PCS	Pain catastrophizing^b^	Total score 0.75 Rumination 0.87 Magnification 0.60 Helplessness 0.79	Low	X	X	X	X
Brief Pain Inventory	BPI	Pain interference and severity	Interference 0.89–0.92 Severity 0.80–0.87	Low	X	X	X	X
Patient Health Questionnaire–9 items	PHQ-9	Depression	Total score 0.87	Low	X	X	X	X
Patient-Reported Outcome Measurement Information System	PROMIS	Physical and psychological health	Mental and physical 0.73–0.96	High	X	X	X	X
Mindful Awareness Attention Scale	MAAS	Mindfulness	Total score 0.87	High	X	X	X	X

*N/A* Not applicable

This table provides the list of questionnaires that will be administered to study participants. Additionally, this table provides details related to when each questionnaire will be administered; the questionnaire’s abbreviation, domain, and psychometrics; and how the questionnaire should be interpreted

^a^Scores representing “improved” functional health status

^b^Primary outcome

Participants will have the option of completing each questionnaire on paper or via an online form. Participants who opt for paper forms will be provided with a packet of questionnaire copies with return envelopes and stamps. Participants who opt for online forms will provide an email address and be emailed hyperlinks that contain exact copies of the paper forms managed by a REDCap database [22]. The order and structure of each measurement will be identical in the paper and online versions. Each assessment packet includes the five questionnaires described in the subsections below. *See* Table 3 for a summary of instruments and schedule of assessments.

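### The baseline window runs from recruitment and does not end at randomization, so a cohort's last consenters may give a valid baseline PCS after allocation

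*Protocol article*

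**What the plan says.** The Feasibility section that lists the measures sets the window. Its sentence begins "Failure to complete measures within 2 weeks of recruitment (baseline", goes on to apply the same limit to MBI sessions 1, 3 and 6, and treats a later form as missing for that time point. For baseline, the clock starts at recruitment.

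Randomization procedures sets two other dates. The trigger for allocation is consent of the cohort: "After the first cohort of 15 participants provides informed consent, they will be randomly assigned either to receive the MBI". The conditions for being randomized are consent and eligibility: "Patients who provide informed written consent and meet the participant selection criteria will be enrolled and randomized using a 2:1 treatment allocation". A returned baseline form is not among them. Treatment then follows: "Within 2 weeks of randomization, participants will begin the MBI or their time in the control condition".

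The Efficacy section with Table 3 adds the only other limit on baseline timing. Questionnaires are given at "week 0 (baseline, prior to initiation of treatment) and weeks 1, 3, and 6". The boundary is the start of treatment, not randomization.

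The same article expects a wait before the start. Cohorts of 15 are used "to reduce the amount of idle time between informed consent and intervention delivery", and Retention strategies and compensation provides weekly contact on how many more participants are needed.

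**The concern.** The PCS total is the primary efficacy outcome. It is self-reported, and the comparator is a wait list with usual care, so the arm is evident once disclosed. A baseline answered after a patient knows the assignment is a post-randomization measurement: expectation or disappointment can move it differently in the two arms, and that difference passes into the change from baseline. The stated purpose of this pilot is to estimate effect sizes, so the affected quantity is its main efficacy product.

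A second, lesser matter comes from the same rule. Someone who consents early must answer within 2 weeks, then waits for the cohort to fill and for up to 2 more weeks before starting. That value is labelled week 0 although it may be much older.

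**Working it through.** The plan gives no figure to reproduce here. The check is date arithmetic.

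**Inputs from the article**
- Baseline window: 2 weeks from recruitment (Feasibility).
- Cohort of 15, randomized after its members consent; start 0 to 2 weeks later (Randomization procedures).
- Allocation 40 to 20 (Setting and sample).

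**Assumptions, not in the article**
- Steady accrual at r = 1, 2 or 4 consents per week.
- Recruitment date equals consent date.
- Randomization takes place at the 15th consent, and treatment starts a full 2 weeks later.
- Those who answer after allocation know their arm, and this shifts their baselines by 0.2 to 0.5 SD between arms.

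**Open windows at randomization.** The i-th consenter waits (15 − i)/r weeks. Those with a wait of at most 2 weeks number 1 + 2r.

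| r per week | At or inside window | Share of 15 | Mean wait 7/r (weeks) | Longest wait 14/r (weeks) |
|---|---|---|---|---|
| 1 | 3 | 20% | 7 | 14 |
| 2 | 5 | 33% | 3.5 | 7 |
| 4 | 9 | 60% | 1.75 | 3.5 |

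Each count includes one patient whose window closes exactly at randomization. Faster accrual raises the count: if a cohort fills in 2 weeks, 14 of 15 windows are still open.

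**Expected late completers.** If completion is uniform over the 2 weeks, a patient with wait w answers after randomization with probability 1 − w/2.
- r = 1: 1 + 0.5 + 0 = 1.5 of 15 (10%).
- r = 2: 1 + 0.75 + 0.5 + 0.25 + 0 = 2.5 of 15 (17%).
- r = 4: nine terms falling evenly from 1 to 0, sum 4.5 of 15 (30%).

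If treatment starts sooner than 2 weeks after randomization, fewer late forms still precede it and these numbers fall.

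**Bias in mean change from baseline** = share answering late × shift.
- Uniform completion: 0.10 × 0.2 = 0.02 SD to 0.30 × 0.5 = 0.15 SD.
- Upper bound, everyone at or inside the window answering late: 0.20 × 0.2 = 0.04 SD to 0.60 × 0.5 = 0.30 SD.

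For scale, the standard error of a standardized difference with 40 and 20 patients is √(1/40 + 1/20) = 0.27. It applies to a change score if the baseline-to-follow-up correlation is 0.5, which is also an assumption. So 0.15 SD is about half a standard error (0.15/0.27 ≈ 0.55).

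**Age of early baselines.** The first consenter answers 0 to 2 weeks after consent, and treatment starts 0 to 2 weeks after randomization. The baseline's age at start is therefore the longest wait plus or minus 2 weeks: 12 to 16 weeks at r = 1, 5 to 9 at r = 2, and 1.5 to 5.5 at r = 4. The two problems move in opposite directions: slow accrual gives old baselines and few late ones, fast accrual the reverse.

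**The case against.** Several points against this have force.

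- **Baseline after session 1.** A reader might infer that a form completed after session 1 still counts, since the 2-week window could extend past it and the first payment, in dollars, is set as "10.00 after baseline assessments are received and/or participation in MBI session 1 has occurred". The documents do not support that. The Efficacy section places baseline before treatment, and the payment sentence governs compensation, not validity. At most it suggests that the form is not required before session 1.
- **Old baselines as bias.** A reader might also infer that stale baselines bias the comparison. Both arms of a cohort are randomized together, so age falls on both alike. It adds noise and, if nominal weeks are used, misplaces the first time point. The article does not fix nominal or actual time, and that may be settled in an analysis plan that is not shown.
- **What is not shown.** Fig. 1 may place baseline before allocation. The article does not say when participants learn their arm, or that randomization follows the 15th consent at once. In-person recruits receive their forms at consent, which suggests that many will answer at entry.
- **Recruitment date.** Phone recruits agree verbally before the consent form is mailed. If recruitment means that agreement, part of their window passes before they count towards the cohort.

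These points limit certainty and size. They do not remove the gap: no text shown ends the baseline window at allocation, and the 15th consenter's window can lie almost wholly after it.

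**Conclusion.** The point holds in this limited form. It concerns a stated rule whose anchor is badly chosen, not a detail left out. Valid baselines can fall between randomization and the start of treatment, and on an unblinded self-report this can bias the between-arm change. The plausible size is about 0.02 to 0.15 SD. The 0.30 SD figure is a ceiling, not an estimate, because it needs every patient at or inside the window to answer late. All of these figures rest on assumed accrual and an assumed shift, neither given in the article, and the direction of the bias cannot be determined from it. The ageing of early baselines is a separate matter of precision and time placement. The change is worth making because the estimate is the purpose of the pilot and the correction is cheap.

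**What to change.** Replace the baseline part of the window rule in Feasibility with one that ends at randomization, for example the 2 weeks before the cohort is randomized. Obtain the form before allocation is disclosed, and reconcile the text with Fig. 1. With that example, no baseline follows allocation, and none is older than 2 + 2 = 4 weeks at the start of treatment, whatever the accrual speed.

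The article reports that recruitment has closed, so for this trial the usable part is analytic. Flag baselines dated after randomization, repeat the PCS analysis without them, and enter each baseline at its actual date in the trajectory model.

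The cost is small. One more prompt is needed as a cohort fills, and weekly contact already exists. A cohort may wait a few days for the last form. Assessment completion is a feasibility measure, so baseline completion should then be reported among consented rather than randomized participants; otherwise the new rule would push it towards 100%.

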### Acceptability

Acceptability will be assessed qualitatively. Semistructured interviews will be performed with ten randomly selected participants from the MBI condition within 2 weeks of the final MBI session by telephone to assess acceptability and help interpret quantitative findings related to the exploratory aim [38]. Each MBI participant who completes at least one MBI session will be randomly assigned a number using the random number function in Excel 2007 and then ordered in an ascending fashion. The participant with the lowest number will be contacted first, followed by the participant with the next lowest number, and so forth. Two to three participants will be selected from among each of the four cohorts. Each interview will be conducted by one study staff member who is familiar with the content of the MBI. The interview will consist of the questions listed in Table 2.

**Table 2 Tab2:** Semistructured postinterview questions

Q1	Tell me about how easy or difficult it was for you to complete the weekly telephone-based MBI sessions?
Q2	What impact, if any, do you feel the MBI program had on (a) your perceptions on chronic pain, and (b) your quality of life?
Q3	What did you find most useful about the MBI program?
Q4	What did you find least useful about the MBI program?
Q5	What would you want more of in the MBI program?
Q6	What would you eliminate or have less of in MBI program?
Q7	Tell me about how easy or difficult it was for you to practice mindfulness, and complete the homework assignments?
Q8	Do you intend to continue using this MBI?
Q9	Would you recommend a MBI to friends with SCD who also experience chronic pain?
Q10	Is there anything else that you would like me to know about your experience?

*MBI* Mindfulness-based intervention, *SCD* Sickle cell disease

This table provides a list of questions that will be asked of study participants who are randomized to the experimental condition, and it will be administered at the end of the 6-week MBI

Because we were unable to find any literature on the subjective experiences of persons with SCD and chronic pain who participated in a mindfulness intervention, the guiding questions listed in Table 2 will be used to roughly structure conversations, allowing digression into other topics brought up by the participants. Interviews will be digitally recorded, and we anticipate that they will last between 30 and 60 minutes.

### Efficacy

To address aim 2, five valid and reliable patient-reported questionnaires will be administered to determine the effects of MBI relative to the control condition on pain catastrophizing, as well as on pain interference and severity, depression, health-related quality of life (mental and physical health), and mindfulness (Table 3). Each questionnaire will be administered at four time points: week 0 (baseline, prior to initiation of treatment) and weeks 1, 3, and 6. Assessments at weeks 1, 3, and 6 correspond to MBI session 1, session 3, and session 6, respectively.

**Table 3 Tab3:** Instruments and schedule of assessments

Instrument	Abbreviation	Domain	Scale/subscale reliability (Cronbach’s α)	Interpretation^a^	Baseline	Week 1	Week 3	Week 6
Demographic Questionnaire	DEMO	Sociodemographic and clinical characteristics	N/A	N/A	X			
Pain Catastrophizing Scale	PCS	Pain catastrophizing^b^	Total score 0.75 Rumination 0.87 Magnification 0.60 Helplessness 0.79	Low	X	X	X	X
Brief Pain Inventory	BPI	Pain interference and severity	Interference 0.89–0.92 Severity 0.80–0.87	Low	X	X	X	X
Patient Health Questionnaire–9 items	PHQ-9	Depression	Total score 0.87	Low	X	X	X	X
Patient-Reported Outcome Measurement Information System	PROMIS	Physical and psychological health	Mental and physical 0.73–0.96	High	X	X	X	X
Mindful Awareness Attention Scale	MAAS	Mindfulness	Total score 0.87	High	X	X	X	X

*N/A* Not applicable

This table provides the list of questionnaires that will be administered to study participants. Additionally, this table provides details related to when each questionnaire will be administered; the questionnaire’s abbreviation, domain, and psychometrics; and how the questionnaire should be interpreted

^a^Scores representing “improved” functional health status

^b^Primary outcome

Participants will have the option of completing each questionnaire on paper or via an online form. Participants who opt for paper forms will be provided with a packet of questionnaire copies with return envelopes and stamps. Participants who opt for online forms will provide an email address and be emailed hyperlinks that contain exact copies of the paper forms managed by a REDCap database [22]. The order and structure of each measurement will be identical in the paper and online versions. Each assessment packet includes the five questionnaires described in the subsections below. *See* Table 3 for a summary of instruments and schedule of assessments.

#### Pain Catastrophizing Scale

The Pain Catastrophizing Scale (PCS) will be used to assess pain catastrophizing. The PCS contains 13 items rated on a 5-point scale from 0 (not at all) to 4 (all the time). The total score for the PCS ranges between 0 and 52, with a higher score demonstrating more severe catastrophizing. In addition, the PCS contains three subscales: helplessness (six items), rumination (four items), and magnification (three items) [39]. The PCS was selected as the primary variable of interest in addressing intervention efficacy because it has been studied extensively across many different chronic pain populations and is commonly used as a key outcome in determining the success of interventions that target chronic pain [40, 41]. A total PCS score of 30 represents a clinically relevant level of catastrophizing and corresponds to the 75th percentile of the distribution of PCS scores in clinical samples of chronic pain patients [42]. The PCS total score was the primary outcome.

#### Brief Pain Inventory

The Brief Pain Inventory (BPI) will be used to assess physical pain. As one of the standard psychometric tools for clinical trials of pain [43, 44], the BPI provides two subscales: pain interference and pain severity. Pain interference (seven items) and pain severity items (five items) are rated on a 0–10 scale, with 10 indicating complete interference or worst possible pain severity. There are no clinical cutoff scores for the BPI, but “worst pain” or the arithmetic mean of the four severity items can be used as measures of pain severity, and the arithmetic mean of the seven interference items can be used as a measure of pain interference.

#### Patient Health Questionnaire–9 items

The Patient Health Questionnaire–9 items (PHQ-9) will be used to assess depression. The PHQ-9 is a multipurpose instrument used for screening, diagnosing, monitoring, and measuring the severity of depression [45]. Consisting of nine items on a Likert scale (0 = not at all, 3 = nearly every day), the measurement provides a severity score for depression (range 0–27) of minimal symptoms (5–9), minor depression (10–14), moderate depression (15–19), or severe depression (20–27).

#### Patient-Reported Outcomes Measurement Information System

The Patient-Reported Outcomes Measurement Information System (PROMIS) [47] global short form will be used to assess physical and mental health. The PROMIS global short form is a ten-item instrument that represents multiple domains developed by the National Institutes of Health. The tool has a total of ten items with a Likert scale (0–5) and generates a global physical health score and a global mental health score [46]. Currently, there are no clinical cutoff scores for chronic pain for PROMIS, but they are currently being developed [47].

#### Mindful Attention Awareness Scale

Mindful Attention Awareness Scale (MAAS) will be used to assess mindfulness. The MAAS measures present moment awareness, interpersonal communication, thoughts, emotions, and physical states. Consisting of 15 items on a Likert scale (1 = almost always to 6 = almost never), the measurement provides a single total score of mindfulness, with a higher score indicating a higher level of mindfulness.

### Analytic approaches

Atlas ti 7™ software (Scientific Software Development, Berlin, Germany) will be used to analyze qualitative data, and SAS version 9.3™ software (SAS Institute, Cary, NC, USA) will be used to conduct statistical procedures for quantitative data and to estimate effect sizes for the efficacy outcomes. When statistical significance testing is conducted, nondirectional tests will be performed, with the level of significance set at 0.05. As noted earlier, the focus of this pilot study is to examine the direction and magnitude of effect of the MBI on primary and secondary outcomes rather than to conduct statistical significance testing.

### Sample characteristics

Descriptive statistics will be used to summarize sociodemographic and clinical characteristics. Nonparametric Wilcoxon two-sample tests will be used to test for differences in continuous sociodemographic and clinical variables between conditions. Chi-square tests will be performed to test for differences in categorical sociodemographic and clinical variables between conditions. A sensitivity analysis will be performed to compare sociodemographic and clinical characteristics between randomized participants who complete at least one assessment at any time point with those who do not complete any outcome assessments (observable cases = no or yes).

